## Abstract

**Background:**

Type 2 diabetes mellitus (DM) is responsible for a significant reduction in the quality of life due to its negative impact on functional capacity. Cardiopulmonary fitness impairment in DM patients has been associated with limited tissue oxygenation. Phototherapy is widely utilized to treat several disorders due to expected light-tissue interaction. This type of therapy may help to improve muscular oxygenation, thereby increasing aerobic fitness and functional capacity.

**Methods/Design:**

This study is a randomized, double-blind, placebo-controlled crossover trial approved by the Ethics Committee of the Federal University of São Carlos and registered at ClinicalTrials.gov. Four separate tests will be performed to evaluate the acute effect of phototherapy. All participants will receive both interventions in random order: light-emitting diode therapy (LEDT) and placebo, with a minimum 14-day interval between sessions (washout period). Immediately after the intervention, participants will perform moderate constant workload cycling exercise corresponding to 80 % of the pulmonary oxygen uptake $$ \left({\mathrm{p}\overset{\cdotp }{\mathrm{V}}\mathrm{O}}_2\right) $$ during the gas exchange threshold (GET). LEDT will be administered with a multidiode cluster probe (50 GaAIA LEDs, 850 ηm, 75 mW each diode, and 3 J per point) before each exercise session. Pulmonary oxygen uptake, muscle oxygenation, heart rate, and arterial pressure will be measured using a computerized metabolic cart, a near-infrared spectrometer, an electrocardiogram, and a photoplethysmography system, respectively.

**Discussion:**

The main objective of this study is to evaluate the acute effects of muscular pre-conditioning using LED phototherapy on pulmonary oxygen uptake, muscle oxygenation, heart rate, and arterial pressure dynamics during dynamic moderate exercise. We hypothesize that phototherapy may be beneficial to optimize aerobic fitness in the DM population. Data will be published after the study is completed.

**Trial registration:**

Registered at ClinicalTrials.gov under trial number NCT01889784 (date of registration 5 June 2013).

## Background

Type 2 diabetes (DM) is a significant health problem worldwide due to its high prevalence and mortality [1]. It is characterized by hyperglycemia caused by defects in insulin secretion and/or insulin action. DM is associated with many well-known chronic comorbidities and complications that compromise many tissues, especially the blood vessels, heart, and nerves [2].

Individuals with DM have reduced aerobic fitness characterized by lower peak pulmonary oxygen uptake $$ \left(p\overset{\cdotp }{V}{O}_2\right) $$ [3–6]. In addition, $$ p\overset{\cdotp }{V}{O}_2 $$ kinetics analysis has been used to characterize $$ p\overset{\cdotp }{V}{O}_2 $$ dynamics during submaximal exercise transitions [5, 7]. The $$ p\overset{\cdotp }{V}{O}_2 $$ kinetics during exercise transitions are related to the cardiorespiratory system’s ability to offer O_2_ and the capacity of the exercising muscle to utilize this O_2_ [5, 7]. DM patients have delayed $$ p\overset{\cdotp }{V}{O}_2 $$ response after the onset of light to moderate exercise [5, 8] and premature muscular fatigue [9] in comparison with a control group. Many potential mechanisms could explain these impaired responses, for example, reduced muscle blood flow [10] and capillary density [11], defects in muscular oxygen diffusion, and lower mitochondrial oxygen utilization [5] and function [9, 12, 13].

Phototherapy is a widely used resource due to its effect on biological tissues, potentially improving muscular efficiency and aerobic fitness [14–18]. Studies with animals have shown enhanced mitochondrial function [19, 20], microcirculation, and tissue oxygenation [21, 22] mediated by phototherapy. Additionally, studies with healthy humans demonstrate improvements in muscular function, fatigue resistance, $$ p\overset{\cdotp }{V}{O}_2 $$, and exercise tolerance [17, 23] and decreased concentrations of lactate and muscle damage markers [23–26].

DM patients have an impaired ability to deliver oxygen (O_2_) to the muscle and possibly to use this O_2_ during exercise, which leads to an imbalance between muscle blood flow and $$ p\overset{\cdotp }{V}{O}_2 $$ [27], resulting in hampered $$ p\overset{\cdotp }{V}{O}_2 $$ dynamics. Therefore, the main aim of this study is to evaluate the acute effects of LED phototherapy on muscle oxygenation and $$ p\overset{\cdotp }{V}{O}_2 $$ kinetics in individuals with DM during moderate cycling exercise. We hypothesize that phototherapy will promote therapeutic effects such as improved aerobic fitness, which could ultimately lead to better functional capacity.

## Methods/Design

### Design

This study is a randomized, double-blind, placebo-controlled crossover trial approved by the Ethics Committee of Federal University of São Carlos (number 13573013.1.0000.5504) and registered at ClinicalTrials.gov under Trial Number NCT01889784. This study will be conducted in accordance with the human research standards set out by the National Health Council Resolution 196/96. The subjects will be included in the study after providing written informed consent.

The subjects will be divided into two groups: DM group (DMG) and healthy group (HG). After screening, the subjects of both groups who meet the eligibility criteria will be randomly allocated to one of two subgroups (A and B) as described in Fig. 1a. Four separate tests will be conducted to evaluate the acute effect of phototherapy. All subjects will receive both interventions, light-emitting diode therapy (LEDT) and placebo, with a minimum 14-day interval between sessions (washout period). The subgroups will determine the intervention order because the interventions will be alternated in each visit (Fig. 1b). The subjects in subgroup A will receive LEDT in the first and third sessions and placebo in the second and fourth sessions. Subjects in subgroup B will receive the reverse order. The researcher responsible for the randomization process will also prepare the LEDT device (effective or placebo) before each visit and will not analyze the data.

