### Data analysis procedures

The $$ p\overset{\cdotp }{V}{O}_2 $$ and NIRS data collected during constant workload exercise will be submitted to time domain kinetics analysis as previously described [5, 32–34]. The data obtained in the two repetitions of the same constant workload protocol for each intervention (LEDT or placebo) will be time-aligned and second-by-second interpolated; then, the point-by-point mean between tests will be finally submitted to kinetics analysis.

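### Strict alternation leaves a linear session trend in every participant's LEDT-minus-placebo difference, and the ANOVA named has no subgroup or period term to remove it

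*Protocol article*

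**What the plan says.** Under Design, participants in the diabetes group and the healthy group "will be randomly allocated to one of two subgroups (A and B". The subgroup fixes the whole order: "The subgroups will determine the intervention order because the interventions will be alternated in each visit". For subgroup A, "The subjects in subgroup A will receive LEDT in the first and third sessions and placebo in the second and fourth sessions"; for the other, "Subjects in subgroup B will receive the reverse order". The two sequences are therefore ABAB and BABA, with A for LEDT and B for placebo. The abstract's phrase, "All participants will receive both interventions in random order", amounts to a random choice between these two. Sessions are held "with a minimum 14-day interval between sessions (washout period", so session 4 falls at least 3 x 14 = 42 days after session 1.

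Under Data analysis procedures, the two repeats of each intervention are aligned and averaged, and "the point-by-point mean between tests will be finally submitted to kinetics analysis". That leaves one result per intervention per participant. Statistical analysis then names a two-way repeated-measures ANOVA with Tukey comparisons. The article does not list the two factors. From the comparisons it announces, I take them to be group (diabetes or healthy) and intervention. Sequence subgroup and period are not mentioned.

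**The concern.** Four exercise tests over six weeks or more can show a drift, for example from familiarisation or a change in fitness. Under alternation, each participant's LEDT sessions lie on average one session earlier (A) or later (B) than the placebo sessions, so a linear drift does not cancel within the person. If the model ignores subgroup, the drift enters the error term, and it enters the estimate itself when the subgroups differ in size. The allocation ratio and subgroup sizes are not given.

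A second matter is carry-over. Every session after the first follows the other intervention, so this order gives little power to tell a residual effect from the direct effect.

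**Working it through.** **Inputs.** From Design: sequences ABAB and BABA, four sessions, at least 14 days apart. From Data analysis procedures: one averaged result per intervention. From Statistical analysis: 5 % significance level and power 0.80. The article gives no sample size, effect size or SD with that power, so there is no figure to reproduce. Assumed for illustration: two-sided test, true effect of 0.5 SD, and trends b of 0.25, 0.5 and 1 SD per session. SD here is that of the participant differences without trend. The algebra is exact for a response averaged over sessions and approximate for parameters fitted to the averaged trace.

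**1. Linear trend within a participant.**
- Subgroup A: LEDT in sessions 1 and 3 (mean 2), placebo in 2 and 4 (mean 3). Difference = tau + b(2 - 3) = tau - b.
- Subgroup B: difference = tau + b(3 - 2) = tau + b.

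**2. Group mean without a subgroup term.** Mean = tau + b(nB - nA)/(nA + nB).
- 10:10 gives 0; 11:9 gives -0.1b; 12:8 gives -0.2b; 14:6 gives -0.4b.
- With b = 0.5 SD and 12:8: 0.5 x (8 - 12)/20 = -0.10 SD.

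**3. Error without a subgroup term.** With equal subgroups the shifts of -b and +b add b² to the variance of the differences, giving 1 + b² in units of SD².
- For n = 20 and b = 0.5: standard error sqrt(1.25/20) = 0.250, against sqrt(1/20) = 0.224.
- Number needed: n = (1.96 + 0.84)² x (1 + b²)/0.5². This is 32 for b = 0, then 34, 40 and 63 for b = 0.25, 0.5 and 1.
- These numbers treat subgroup membership as random. If a 10:10 split is forced, the mean itself varies no more than before and the reported error is simply too large, so the loss of power is somewhat smaller.

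**4. With subgroup x intervention, equal weights.** Half of (tau - b) + (tau + b) equals tau. The same cancellation holds for any period effect common to both subgroups, because they are mirror images.
- Standard error = sqrt(0.25 x (1/nA + 1/nB)). For 10:10 this is 0.224; for 12:8 it is 0.228. The difference is the price of unequal subgroups when there is no trend.

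**5. Carry-over.** Let lambda be the carry-over of LEDT minus that of placebo (L and P below).
- ABAB: LEDT sessions carry (0 + P)/2 and placebo sessions carry L, so the bias is P/2 - L. BABA: P - L/2. The average is -0.75 lambda.
- ABBA: -L/2. BAAB: P/2. The average is -0.25 lambda.
- Variance of the LEDT effect by least squares with participant and period effects, one participant per sequence, in units of the within-session variance:

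| Sequences | No carry-over term | With carry-over term | Efficiency |
|---|---|---|---|
| ABAB/BABA | 0.50 | 2.75 | 0.50/2.75 = 18 % |
| ABBA/BAAB | 0.50 | 0.55 | 0.50/0.55 = 91 % |

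**The case against.** The design already does much of the work. Randomised mirror-image subgroups remove any common period effect from the group mean when they are equal in size. This stands: the residual problem is a larger error term, plus bias only under imbalance.

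A reader might infer more than the article supports:
- **That any time trend survives.** It does not. A centred quadratic pattern (1, -1, -1, 1) or a step between sessions 2 and 3 cancels in each alternating sequence. The quadratic pattern does not cancel under ABBA/BAAB, where it leaves +2 and -2.
- **That ABBA/BAAB avoids the problem.** It removes the linear trend but leaves -0.25 lambda of carry-over bias.
- **That carry-over cannot be separated at all.** It can be estimated from per-visit data, at low efficiency. After the planned averaging it cannot be separated under either order, so the fivefold variance (2.75 against 0.55) belongs to an analysis that is not planned.
- **That alternation is the worst choice on every count.** AABB/BBAA leaves twice the linear trend (sessions 1 and 2 against 3 and 4: -2b and +2b), though its carry-over-adjusted variance is 0.55.
- **That alternation in particular weakens blinding.** Any scheme of two mirrored sequences reveals all sessions once one is identified, and ABBA/BAAB is such a scheme.

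It is also fair to say that the effect studied is acute and the sessions are at least 14 days apart, so lambda may be near zero. The article offers no evidence on how long the effect lasts, so this remains an assumption. Finally, a fuller analysis plan may already contain a subgroup or period term; if so, only the limitation on carry-over remains.

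**Conclusion.** The point holds as an analysis matter. The sequences are fixed as ABAB/BABA, and the ANOVA as named leaves a linear trend of -b or +b in the differences. At b = 0.5 SD per session, the standard error with 20 participants rises by about 12 % (0.250/0.224), and a 12:8 split adds a bias of -0.10 SD. At b = 0.25 SD the cost is small (34 participants instead of 32). The size of b, the number of participants and the subgroup split are assumptions, since the article gives none of them.

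The carry-over weakness is real but conditional: a bias of -0.75 lambda that the planned analysis cannot detect, and that is zero if the washout works. It does not justify a new allocation in this trial. Recruitment is under way (Trial status) and the diabetes group is tested before the healthy group (Subjects). Changing the order only for later participants would largely tie the sequence scheme to the group comparison. With full separation, unmodelled carry-over would then produce a false group-by-intervention difference of 0.75 lambda - 0.25 lambda = 0.5 lambda.

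**What to change.** Before the data are unblinded:

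1. Keep the present allocation for all participants, healthy group included.
2. Add randomised subgroup (A/B) and its interaction with intervention to the repeated-measures model, and estimate the LEDT effect as the equally weighted average over the two subgroups. Where trends may differ between the diabetes and healthy groups, let the interaction differ by group. This works on the averaged data as planned. A period term on kinetics fitted to each visit is an alternative, but it gives up the averaging of repeats before the fit.
3. Report the number of participants per subgroup within each group.
4. State as a limitation that alternation gives 18 % efficiency for a carry-over-adjusted LEDT effect (91 % under ABBA/BAAB), that unmodelled carry-over would bias the estimate by -0.75 lambda, and that the conclusion therefore relies on the washout.

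The cost is one or two degrees of freedom and, if the subgroups are unequal and there is no trend, slightly lower precision (standard error 0.228 instead of 0.224 SD at 12:8). No visit, measurement or participant is added.

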**Fig. 1 Fig1:**
[figure not shown]
Study design flowchart. Screening and group/subgroup allocation are described in **a**. The intervention order of the study is described in **b**. DMG, diabetes mellitus group; HG, healthy group

### Subjects

All subjects must be free of overt coronary disease, and they must be between 40 and 64 years of age. DM individuals must have a diagnosis according to the recommendations of the American Diabetes Association [2]. The groups will be matched by age and body mass index (BMI). To achieve that, we will first screen and test the DMG, then evaluate the control group matching age and BMI.

Exclusion criteria are BMI > 35 kg/m^2^, high-sensitivity C-reactive protein (hs-CRP) > 3.0 mg/L, smoking, anemia, alcoholism, use of anti-inflammatory or inhalable drugs, known respiratory and inflammatory diseases, congestive heart failure, and disability conditions that preclude exercise. Healthy subjects will be excluded if they have direct family members with DM.

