### Statistical analysis

The data will be expressed as mean and standard deviation values. The Kolmogorov-Smirnov and Levene tests will be used to test the data for Gaussian distribution and variance, respectively. The statistics analysis will be performed using two-way repeated-measures ANOVA and a post hoc Tukey test for intergroup, intragroup, and multiple comparisons. The level of significance will be set at 5 % (p < 0.05). The statistical power will be set at 0.80, which is the minimal value recommended in the literature to minimize type II error.

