## Discussion

The chronic effect of phototherapy has been widely studied and shows promising results related to increased peak $$ p\overset{\cdotp }{V}{O}_2 $$, reduction in fatigue, and lactate and C-reactive protein concentrations [23, 24–26]. This novel therapeutic tool is generally studied in healthy participants [17, 18, 23, 25, 26]; however, the acute effects of phototherapy are still unknown in DM and its impact on $$ p\overset{\cdotp }{V}{O}_2 $$ dynamics still needs further clarification.

The effects of LEDT could be beneficial to the DM population because the exercise intolerance of this population decreases quality of life and further increases cardiovascular risk. Therefore, the purpose of this randomized clinical trial is to evaluate the acute effects of LEDT on $$ p\overset{\cdotp }{V}{O}_2 $$ dynamics in subjects with DM and healthy age- and sex-matched subjects. The results will elucidate the effects of LEDT and may support the use of this therapy in individuals with DM.

Data will be published after the study is completed.

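### Healthy controls are matched to the DM group on age and BMI, but the stated ANOVA carries no term for these factors, so the DMG versus HG comparison gives up some precision (minor)

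*Protocol article*

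**What the plan says.** Under Subjects, the Protocol article states "The groups will be matched by age and body mass index (BMI") and describes the order of work: "we will first screen and test the DMG, then evaluate the control group matching age and BMI". It does not say whether this means one-to-one pairs or balancing the groups as a whole, and it gives no tolerance.

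The Discussion names different factors. It refers to "subjects with DM and healthy age- and sex-matched subjects", so BMI has gone and sex has appeared.

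Under Statistical analysis: "The statistics analysis will be performed using two-way repeated-measures ANOVA and a post hoc Tukey test for intergroup, intragroup, and multiple comparisons". The factors of the ANOVA are not named. I read them as group (between persons) and intervention (within persons). No matching term and no age or BMI covariate is mentioned. The same section sets a 5% significance level and says "The statistical power will be set at 0.80", without a sample size, effect size or standard deviation.

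The main aim, in the Background, concerns the intervention: "the main aim of this study is to evaluate the acute effects of LED phototherapy on muscle oxygenation" and on oxygen uptake kinetics in people with DM. It is addressed within persons, because "All subjects will receive both interventions".

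**The concern.** Choosing controls to resemble the DMG on age and BMI removes variation in those two factors from the difference between the groups. If they predict the outcome, the outcomes of the two groups become positively correlated. An ANOVA that treats the groups as independent samples leaves that variation in its error term. The group difference is then estimated more precisely than its reported standard error shows.

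What is at stake is efficiency in the DMG versus HG comparisons of level, for example in oxygen uptake kinetics or muscle oxygenation. Confidence intervals would be wider than they need be, and a real group difference would be somewhat easier to miss. The article fixes the method for these intergroup tests, so this concerns a stated choice and not merely a detail left out.

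**Working it through.** **Inputs from the Protocol article.** Matching on age and BMI (Subjects); two-way repeated-measures ANOVA with Tukey tests, 5% level, power 0.80 (Statistical analysis). The stated power cannot be reproduced, because no N, effect size or standard deviation accompanies it.

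**Assumptions.** Two-sided test; n = 10, 15 or 20 per group; rho = 0 to 0.5. Here rho is the correlation that matching induces between the groups. Under close matching it equals the share of outcome variance explained by age and BMI. The standardised difference d is set so that an unmatched t-test has 0.80 power at rho = 0: d = 1.325, 1.060 and 0.909 for n = 10, 15 and 20. With one mean per participant, the between-group test of the ANOVA is equivalent to this t-test.

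**Step 1: standard error.** True variance of the group difference = 2σ²(1-rho)/n. Variance estimated without adjustment = 2σ²/n. The ratio of standard errors is 1/sqrt(1-rho): 1.054, 1.118, 1.195 and 1.414 at rho = 0.1, 0.2, 0.3 and 0.5.

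**Step 2: type I error and power.** The unadjusted test was simulated 40,000 times per setting. Power of the adjusted test comes from the noncentral t with noncentrality d·sqrt(n/(2(1-rho))) and 2n-4 degrees of freedom, two being spent on covariates. For n = 15 the noncentrality at rho = 0.3 is 1.060 × sqrt(15/1.4) = 3.47 on 26 degrees of freedom.

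| rho (n = 15) | Type I error, unadjusted | Power, unadjusted | Power, adjusted | Change |
|---|---|---|---|---|
| 0 | 0.049 | 0.800 | 0.798 | -0.2 points |
| 0.1 | 0.038 | 0.812 | 0.838 | +2.6 |
| 0.2 | 0.029 | 0.824 | 0.878 | +5.4 |
| 0.3 | 0.021 | 0.839 | 0.916 | +7.7 |
| 0.5 | 0.0075 | 0.873 | 0.977 | +10.4 |

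At rho = 0.1, 0.2, 0.3 and 0.5 the gains are 2.4, 5.3, 7.6 and 10.7 points for n = 10, and 2.8, 5.4, 7.8 and 10.2 for n = 20. At rho = 0 the cost is 0.5 points for n = 10 and nil for n = 20. A separate simulation with two covariates and both exact and inexact matching gave the same picture: gains of about 2-3, 5, 8 and 10-11 points, and a cost of 1 point or less.

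**Step 3: which contrasts are affected.** Take n = 15 and unit variance, split into 0.3 for the matched factor, 0.4 for other differences between persons and 0.3 for residual.

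- *Group difference in participant means.* Variance per participant = 0.3 + 0.4 + 0.3/2 = 0.85. Unadjusted standard error = sqrt(2 × 0.85/15) = 0.337. True standard error = sqrt(2 × 0.55/15) = 0.271. Simulated: 0.337 against 0.269, an overstatement of 25%.
- *LEDT minus placebo within a group.* The matched factor cancels: sqrt(0.6/15) = 0.200. Simulated: 0.200 estimated against 0.202 true.
- *Group x intervention.* It cancels again: sqrt(2 × 0.6/15) = 0.283. Simulated: 0.283 estimated against 0.286 true.

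**Step 4: a pair term instead of covariates.** It leaves n-1 degrees of freedom. At rho = 0 and n = 15, power falls from 0.800 to 0.770. It breaks even only at rho of about 0.1 (0.812 both ways). At n = 8 the break-even point is about 0.2.

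**The case against.** The strongest defence is that this is a short article. Covariates are often left to an analysis plan, and an unadjusted repeated-measures ANOVA is a valid, conservative test. The affected comparison is non-randomised and secondary to the within-person question. The first part stands only in part: the article does name a method for intergroup tests, and that method does not use the matching it describes. The rest stands and sets the severity.

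A reader might infer more than the documents support, in four ways.

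- **That power is certainly lost.** This depends on how strongly age and BMI predict the outcomes among people aged 40 to 64 with BMI up to 35. The documents do not say, and the loss could be negligible.
- **That the trial falls short of 0.80 power.** If the effect is set so that a matched-pair test has 0.80 power, then with 15 per group and rho = 0.5 the unadjusted test has only 0.55. The plan proposes no matched-pair test, however. Its 0.80 stands beside the ANOVA. Measured from an unmatched test, as in Step 2, power stays at about 0.80 or above, and what is forgone is an additional gain.
- **That the treatment effect is compromised.** Step 3 shows that the LEDT versus placebo contrast is untouched, and so is group x intervention if age and BMI act additively.
- **That a paired analysis is required.** The text also fits group matching, in which case no pairs exist.

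**Conclusion.** The point holds as a minor loss of efficiency confined to the DMG versus HG comparison of levels. Controls are selected on age and BMI, and the stated analysis makes no use of it. To the extent that these factors matter, standard errors are too wide by 1/sqrt(1-rho), and type I error falls to about 0.04, 0.03, 0.02 and 0.01 when they explain 10, 20, 30 and 50% of the variance. The power forgone is about 2-3, 5, 8 and 10 points respectively.

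These figures rest on an assumed 10 to 20 per group, an assumed correlation, and group being a between-person factor. The group difference is not biased by leaving out the matched factors, and false positives are not increased. The conflict between Subjects and Discussion over the matching factors needs no assumption. It has to be settled first, because it decides which covariates belong in the model.

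**What to change.** In the Statistical analysis section, specify for the DMG versus HG comparison a mixed model with a participant random effect; group, intervention and group x intervention as fixed effects; and the matching factors as covariates (age and BMI as Subjects now reads). Report the group difference and its confidence interval from that model. The LEDT versus placebo contrast stays within participant.

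Reconcile Subjects (age and BMI) with the Discussion (age and sex), so that the covariates are the factors actually used, and state whether matching is one-to-one or by group. Do not use a pair term unless matching is one-to-one and the correlation is material.

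The cost is two degrees of freedom and a change of wording. Age and BMI are already needed for eligibility and matching, so no new data or participants are required.

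### The diabetic group is tested before the healthy group, so the planned comparison between the two groups is confounded with testing period

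*Protocol article*

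**What the plan says.** Under Subjects, the groups are to be matched on age and BMI, and to achieve this the investigators write: "we will first screen and test the DMG, then evaluate the control group matching age and BMI". No other reason is given for the order. Under Design, membership of DMG or HG is disease status. Only the order of interventions (subgroup A or B) is randomised, and this is done in both groups. On that order: "The subjects in subgroup A will receive LEDT in the first and third sessions and placebo in the second and fourth sessions". For subgroup B the two interventions are swapped. Sessions are at least 14 days apart.

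Under Statistical analysis, the plan is a two-way repeated-measures ANOVA with "a post hoc Tukey test for intergroup, intragroup, and multiple comparisons", so a comparison between the groups is a planned result. The Background states the main aim as the acute effect of LEDT in people with diabetes. The Discussion states the purpose for both diabetic and healthy participants.

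**The concern.** The contrast between DMG and HG is not randomised, so nothing in the design protects it from whatever differs between the two testing periods: season, staff experience, the state of the NIRS equipment. Matching on age and BMI balances the people, not the period in which they were measured. If HG is measured after DMG, the observed difference is the true difference plus the change over time. The ANOVA as described has no term that would remove that change.

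The order is also avoidable. To match a control, the investigators need to know the age and BMI of that control's diabetic counterpart. They do not need the whole diabetic group to have been tested.

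**Working it through.** **No figure in the plan to reproduce.** Statistical analysis sets power at 0.80 but gives no sample size, effect size or SD, so the figures below rest on assumptions, which are marked.

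**1. Group and period.** Code group as 0 for DMG and 1 for HG, and testing period as 0 for the first block and 1 for the second. With sequential testing the two columns are identical, so the matrix [1, group, period] has rank 2, not 3. The expected group difference is the true difference plus the drift between blocks.

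**2. Size on an assumed schedule.** If the 14-day minimum applies between all consecutive sessions, the four sessions span at least 3 × 14 = 42 days. Assume 20 per group, 300 days of enrolment per group, and HG enrolment starting when the last DMG participant finishes. HG dates then lie on average 300 + 42 = 342 days later. A drift of 1 unit per year, with no true effects, gives a spurious HG − DMG difference of 342/365 = 0.94 units (0.938 by simulation). With both groups enrolled over the same 300 days, the simulated figure is 0.001.

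**3. Test date in place of period.** Date varies within each group, so [1, group, date] has rank 3 and a linear drift can be removed. The variance of the group difference is then inflated by about 1 + (342/2)²/(300²/12) = 1 + 29,241/7,500 = 4.9. The adjustment is right only if the drift has the assumed shape. A step between the blocks would stay inside the group difference.

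**4. Interaction.** The contrast here is (LEDT − placebo) in HG minus (LEDT − placebo) in DMG.

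- With sessions at days 0, 14, 28 and 42, subgroup A has mean LEDT date (0 + 28)/2 = 14 and mean placebo date (14 + 42)/2 = 28, a gap of −14 days. Subgroup B has +14 days.
- If A and B are equal in number in each group, the gaps cancel, and drift common to both kinds of session adds 0 to the interaction.
- If A:B were 60:40 in DMG and 40:60 in HG, the net gaps are −2.8 and +2.8 days. At 1 unit per year the spurious interaction is 5.6/365 = 0.015 units.
- If the LEDT effect itself fell by 1 unit per year, the spurious interaction would be −342/365 = −0.94 units. With concurrent testing it is −0.001.

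**5. False-positive rate of a group test.** For a two-sided two-sample t test at 5% with n per group, no true difference and drift d in SD units, the noncentrality is d√(n/2) on 2n − 2 degrees of freedom. For example, n = 10 and d = 0.5 gives 0.5 × √5 = 1.118 on 18 degrees of freedom.

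| n per group (assumed) | d = 0.2 | d = 0.3 | d = 0.5 |
|---|---|---|---|
| 10 | 0.071 | 0.097 | 0.185 |
| 15 | 0.083 | 0.125 | 0.262 |
| 20 | 0.095 | 0.152 | 0.338 |

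The rate rises with n, so recruiting more participants does not cure the problem.

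**The case against.** The strongest reply is that this is a crossover. Every participant receives LEDT twice and placebo twice in alternation, so the control for LEDT is the same person's placebo over the same weeks. That stands. It protects the main aim completely from the order of the groups, and it protects the interaction from any drift that moves both kinds of session alike.

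A reader might infer that the interaction is as fully confounded with calendar time as the group difference, or that LEDT is being judged against historical controls. The Design section does not support either reading. A reader might also infer that no covariate could separate group from time. That is too strong, because test date can do so under an assumed shape of drift, at a cost in precision.

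The article also contains safeguards. Under Measurements, the metabolic cart is calibrated for each session and the lactate and glucose analyser is calibrated too. Under Protocol, all tests are held in the morning at the same time of day. These limit drift in oxygen uptake and blood values. No calibration statement is made for NIRS, and calibration does not remove season or staff learning. A constant offset or gain error would leave a fitted time constant unchanged, because it rescales the amplitude and shifts the baseline only. Amplitudes and the tissue saturation index have no such protection.

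Finally, the size is hypothetical. Nothing in the article supports a particular drift. The table is for a simple two-sample test, not the planned ANOVA. Its null of no group difference is doubtful, since the Background already reports slower oxygen-uptake kinetics in diabetes. Bias in the estimated difference may therefore matter more than false positives. Nor does the article say outright that the last DMG participant finishes before the first HG participant starts, though that is the plain reading.

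**Conclusion.** The point holds for the DMG against HG comparison. As the order is written, that planned contrast is confounded with testing period, and separating the two would rest on an assumed shape of drift. It does not extend to the within-participant LEDT effect in diabetes. It reaches the group-by-LEDT interaction only through a change over time in the LEDT effect itself, such as a change in LED output.

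The bias equals the drift between the blocks, which the documents do not let us estimate. The false-positive rates of about 7 to 19% (10 per group) and 10 to 34% (20 per group) show what drifts of 0.2 to 0.5 SD would do. They are not a forecast. Because the main aim is spared and the remedy is cheap, this is an avoidable weakness in a planned comparison, not a fault that undermines the trial.

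**What to change.** Replace the sequential order under Subjects with rolling or small-block matching. Once a diabetic participant, or a small block of them, has been screened, recruit controls matched on age and BMI and test them in the same calendar window. Record the date of every session and the device checks, including NIRS and LED output.

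The Trial status section says that recruitment is under way, so the order may still be open to change. Where diabetic testing is already complete, keep the record of dates and device checks, and report the contrasts between DMG and HG as non-concurrent.

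The change needs no extra visits and no larger planned sample. Its price is that two recruitment streams run together, and that an occasional control loses the match when a diabetic participant drops out.
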